**Safety data**

Safety data will be listed and summarized. Adverse events will be reported in a table similar to the one below, described as proportions with 95% confidence intervals.

[figure not shown]

[figure not shown]

##### ESTIMATED SAMPLE SIZE

**Intention-to-treat (ITT) population:** all randomized participants

Sample size is calculated for the primary endpoint (prevalence ratios of **high responders at six months after 2nd vaccination with Prevenar**, comparing the two vaccination scheme groups). Setting the probabilities of Type I and Type II error to:

- Type I error probability (a) = 0.05 (two-sided).
- Type II error probability (ß) = 0.20 (power = 1 - ß = 0.80).
- Primary endpoint: proportion of vaccine highresponders (defined as2-fold increase and IgG levels ≥1 µg/mL to at least 5 of 7 pneumococcal serotypes).
- N is the number of participants needed in each group.

| Control\CpG | 0.50 | 0.55 | 0.60 | 0.65 | 0.70 |
| --- | --- | --- | --- | --- | --- |
| 0.20 | 39 | 29 | 23 | 18 | 15 |
| 0.25 | 58 | 41 | 31 | 24 | 19 |
| 0.30 | 93 | 61 | **42** | 31 | 24 |
| 0.35 | 170 | 96 | 62 | 43 | 31 |
| 0.40 | 388 | 173 | 97 | 62 | 42 |

Assuming a prevalence of 30% in control vaccine the group and a prevalence of 60% in the experimental vaccine group a sample size of 42 patients per group is required to detect a difference in prevalence estimated by Poisson regression. The expected drop-out percentage is set to 10%. Thus, a total of 94 subjects are needed in the study.

In accordance with the approach recommended by regulatory authorities, the two-sided 95% confidence interval (CI) of the immune response difference will be calculated.

Should the targeted number of participants not be reached within 12 months from study initiation the primary investigator can decide to stop the study if he considers reaching the expected 94 patients unlikely under the given circumstances. In that case all statistical analysis will then be based on the number of patients included at the time of study termination.

##### ACCESS TO CRFs, PARTICIPANT RECORD AND STUDY RELATED DOCUMENTS

For monitoring, auditing and/or inspection purposes access to CRFs, participant medical records and all study related documents will be granted promptly (by the primary study investigator and/or the scientific advisor) if requested by the study monitor unit, Danish Medicines Agency and/or Regional Ethical comitée.

##### STUDY QUALITY CONTROL AND ASSESSMENT

It is the Sponsor’s responsibility to plan and ensure that the study is conducted according to Good Clinical Practice guidelines, the 1996 version of the Declaration of Helsinki andDanish ethical and legal authority regulations. This implies thorough registering and reporting data according to the CONSORT guidelines{{87 Moher,D. 2001; }}.

It is the Sponsor’s responsibility to establish and maintain a quality control system that guarantees the quality in all aspects of the study.

##### ETHICAL CONSIDERATIONS

Applications to the Danish Data Protection Agency, Regional Ethical committee and Danish Medicines Agency will be submitted. The 23-valent polysaccharide pneumococcal vaccine (i.e. Pneumo Novum) has been on the market since early 1980’s and has been very well tolerated in both immunocompetent and immunocompromised individuals. Only some minor adverse effects (local swelling, nausea, local erythema) and very few serious adverse have been reported even in severely immune compromised patients. The 7-valent conjugated pneumococcal vaccine (Prevenar) has been part of the American children vaccination program since 2000 and several Western European countries have since followed (in accordance with WHO recommendations). Post-marketing surveillance and vaccine trials (including trials on both HIV-positive children and adults) have shown that the vaccine is very well tolerated{{21 Madhi,S.A. 2005;20 Madhi,S.A. 2005; 80 Lockhart,S.P. 2006; 22 Klugman,K.P. 2003; 3 Kamchaisatian,W. 2006; 15 Feikin,D.R. 2001; }}. We therefore consider it unlikely that the vaccines will cause more than minor temporally discomfort. In the background section of this protocol and in the investigator’s brochure (APPENDIX 1) we have discussed the safety of TLR9-agonists. In general the safety of TLR9-agonists has been very good in all trials with TLR9-agonists. At low doses in vaccine trials (like the 1 mg planned in this study) there seems to be a slight increase in the frequency of injection site reactions relative to vaccine alone, but not increased severity as these are generally mild. The clinical experience to date indicates that CPG 7909 treatment (and TLR9-agonist treatment in general) of normal humans, cancer patients or individuals infected with HIV or Hepatitis C does not induce autoimmune disease, kidney disease, liver disease, spleen or bone marrow disease. In all the studies of TLR9-agonist the maximal tolerated dose in humans has never been reached. Therefore a dosing of 1 mg CPG 7909 with each pneumococcal vaccination appears safe and well below the upper limit used in other TLR9-agonist trials. The benefit for all study participants who receive all study vaccinations is that they receive the most effective pneumococcal vaccination known at present time. Our hypothesis is that TLR9-agonist adjuvanted pneumococcal vaccination will substantially improve the magnitude and duration of seroprotection in HIV-infected individuals; thereby reducing morbidity and mortality caused by pneumococcal disease. Thus, on a individual level participants reduce their risk of pneumococcal infection and on a larger scale they contribute to our knowledge of TLR9-enhanced pneumococcal vaccination. Not only HIV-patients; but also elderly, cancer patients and other immune compromised individuals could benefit from this vaccination approach in the future.

##### WRITTEN CONSENT AND PARTICIPANT INFORMATION

Study participants will be recruited when they come for their regular HIV treatment control at the HIV treating center. Written consent will only be obtained after a thorough patient oral and written information has been given by the investigator. If the individual wishes to have more time to consider his or her study participation, he or she can take the information home and contact the study center when a decision has been made.

##### DATA HANDLING AND MANAGEMENT

Blood samples will not be labelled with information that directly identifies the subject but will be coded with the study identification number for the subject.

Samples collected may only be used for the purposes described in this protocol.

Any sample testing will be done in line with the consent of the individual subject.

CRFs and results from blood samples will not be labelled with information that directly identifies the subject but will be coded with the study identification number for the subject. They will be kept in a locked room where access is restricted to study investigators. The investigators are responsible for the data are handled carefully and according to the Danish Data Protection Agency, Regional Ethical committee and Danish Medicines Agency regulations.

The subject identification code will be kept separate from the above subject related information. Access to the identification code is restricted to the primary study investigator and sponsor.

After completion of data collection, all data and participant samples will be entered into a database and the study identification number for the subject will be entered without further information that could directly identify the subject. The identification list identifying each subject by name and Danish Civil Registry Number will be kept in a safe at another location in the Department of Infectious Diseases, Skejby Hospital. Blood samples will be destroyed after completion of all primary and subanalysis. Study data will be available for inspection 10 years after study completion.

##### FINANCING

The study receives no financial support from any of the involved medical companies (Sanofi Pasteur, Wyeth or Coley Pharmaceutical Group). The principal investigator and co-authors of this protocol have no financial interest in the above mentioned companies and receive no personal funding from them during the study. The main funding for the study is achieved thru private fundings and The Clinical Institute at Aarhus University. The laboratory analysis are paid for by the Department of Infectious Diseases, Skejby Hospital. Statens Serum Institute and Flow Applications, Inc. contribute to study financing by offering discounted prices for their laboratory analysis. A “Clinical Trial Agreement” is signed with Coley Pharmaceutical Group who provides CPG 7909 for the study free of charge.

##### PARTICIPANT INSURANCE

All participants are covered through the Danish national patient insurance, through the law of financial compensation from damage due to medicinal products and can also request compensation for personal injuries or sequela from medical research projects.

##### TRIAL REGISTRATION

The trial will be registered on www.clinicaltrials.gov where details of the study and a synopsis will be made publicly available.

# PROTOCOL SYNOPSIS

*Title:* ****Immune Response to**** Toll-like receptor 9-agonist adjuvanted ****Pneumococcal Vaccination in HIV Infected Adults****

*****Indication/Study population:* Immunization of HIV-infected individuals on HAART using a regimen of two conjugated pneumococcal vaccines (Prevenar) and one polysaccharide pneumococcal vaccine (Pneumo Novum) with or without CPG 7909.****

*Rationale*: Pneumococcal disease is a major source of morbidity and mortality in HIV-patients. HIV-patients are vaccine hyporeponders. A good immune response to pneumococcal vaccination enhances vaccine effectiveness, thereby preventing the morbidity and mortality caused by pneumococcal disease. Even when a prime-boost regimen containing both conjugated and polysaccharide pneumococcal vaccine is used, only 13% of the immunized HIV patients are high responders at week 96. Recent data indicate that TLR9-agonists have excellent vaccine adjuvant potential and are safe to use in immunocompetent as well as immunocompromised individuals. The aim of this study is to evaluate the qualitative and quantitative i****mmune** **response to pneumococcal vaccination with or without CpG7909 in HIV-infected adults.****

*Primary efficacy parameter:* 1) Quantitative measurement of specific anticapsular antibodies (7 serotypes)

*Secondary efficacy parameters* 1) Functional activity of specific anticapsular antibodies (pneumococcal serotypes 6B, 14, 19F and 23F) 2) Safety/Tolerability measured by:Adverse events (AEs), Serious adverse events (SAEs), Laboratory tests (hematology, clinical chemistry i.e. viral load (HIV RNA) and CD4-count), Physical examination 3) pneumococcal colonization

# **APPENDIX LIST**

****1.**** Investigator’s brochure

2. ****Common toxicity criteria****

3. CIOMS form

4. Participant diary

# SCHEDULE OF ASSESSMENTS/PROCEDURES

| **Assessments/ Procedures** | **Baseline** | **Vaccination** | | | **Follow-up** | | | |
| --- | --- | --- | --- | --- | --- | --- | --- | --- |
| **Study Day** | **Predose** | **Day 0 (1)** | **Day 90 ± 14 (2)** | **Day 270 ± 30 (2)** | **Day 90 ± 14 (3)** | **Day 270 ± 30 (4)** | **Day 300 ± 30 (4)** | |
| Written Informed Consent | X |  |  |  |  |  |  | |
| Inclusion/Exclusion Criteria | **X** |  |  |  |  |  |  | |
| Medical History and Demographics | **X** |  |  |  |  |  |  | |
| Pregnancy Test**(5)** | **X** |  | **X** | **X** |  |  |  | |
| Randomization | **X** |  |  |  |  |  |  | |
| Conjugate pneumococcal vaccine ± CPG 7909 **(6)** |  | **X** | **X** |  |  |  |  | |
| Polysaccharide pneumococcal vaccine ± CPG 7909 **(6)** |  |  |  | **X** |  |  |  |  |
| **Safety** |  |  |  |  |  |  |  | |
| Physical Examination |  | **X(7)** | **X(7)** | **X(7)** | **X(8)** | **X(8)** | **X(8)** | |
| Bloodpressure and Heartrate |  | **X(7)** | **X(7)** | **X(7)** | **X** | **X** | **X** | |
| Lab Safety Tests**(9, 10)** | **X** |  |  |  | **X** | **X** | **X** | |
| HIV Control Parameters**(11)** | **X** |  |  |  | **X** | **X** | **X** | |
| Adverse Events**(12)** |  | **X** | **X** | **X** | **X** | **X** | **X** | |
| **Efficacy** |  |  |  |  |  |  |  | |
| Functional antibody response | **X** |  |  |  | **X** | X | X | |
| Quantitative antibody response | **X** |  |  |  | **X** | **X** | **X** | |
| Oropharyngeal swap | **X** |  |  |  |  | **X** | **X** | |
| Immunologic markers **(13)** | **X** |  |  |  | **X** | **X** | **X** | |

1. Day 0 vaccination is conducted after all baseline assessments/procedures are made.
2. Day 90 follow-up and vaccination can vary by 14 days
3. Follow-up is done before proceeding to 2nd vaccination
4. Follow-up day 270 and day 300 is allowed to vary by 30 days.
5. Women of childbearing potential only.
6. According to randomization.
7. Participants asked to stay in for at least ½ hour post-vaccination. A physical examination incl. BP and HR will be made before discharge.
8. Physical examination will be made on participants request or if the investigator finds it relevant.
9. Complete bloodcount, serum chemistry and liver parameters
10. If a participant withdraws prematurely, lab safety tests must be done within approximately one week of participant withdrawal
11. Viral load (HIV RNA) and CD4-count
12. Intensity of adverse events graded according to common toxicity criteria (CTC version 2.0).
13. Immunologic markers (i.e. sCD163) that may predict antibody response and cellular immune response.

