##### PROCEDURES:

Consenting participants that pass the inclusion/exclusion criteria will be enrolled in the study. Blood samples for baseline parameter measurements will be drawn before proceeding to immunization.

At randomization, participants will be allocated 1:1 one of two study regimens:

- **Experimental group**: Double paediatric dose of 7-valent conjugate pneumococcal vaccination (Prevenar®, Wyeth) + 1 mg CPG 7909 (day 0), double paediatric dose of 7-valent conjugate pneumococcal vaccination (Prevenar®, Wyeth) + 1 mg CPG 7909 (day 90) and single dose of 23-valent polysaccharide vaccine (Pneumo Novum®, Sanofi Pasteur MSD) + 1 mg CPG 7909 (day 270)
- **Control group**: Double paediatric dose of 7-valent conjugate pneumococcal vaccination (Prevenar®, Wyeth) + 100 μl of placebo (day 0), double pediatric dose of 7-valent conjugate pneumococcal vaccination (Prevenar®, Wyeth) + 100 μl of placebo (day 90) and single dose of 23-valent polysaccharide vaccine (Pneumo Novum®, Sanofi Pasteur MSD) + 100 μl of placebo (day 270).

Blood samples are drawn and follow-up by the physician includes physical examination and medical history, registration of AEs/SAEs, vaccination history outside the study and any other information that may be relevant to document in the CRF. A concluding visit is scheduled at day 300.

A subject who returns for the concluding visit or is available for the concluding contact foreseen in this protocol is considered to have completed the study.

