##### VACCINES AND TEST DRUG/PLACEBO INJECTIONS:

All subjects are dosed at 0, 90 and 270 days. All immunizations are done in the deltoid muscle of the right or left arm (according to the participants preference).

- At day 0 and 90 study participants receive one intramuscular injection of double the recommended paediatric dose of Prevenar 1.0 ml + 0.1 ml test drug (CPG 7909)/placebo. In both cases, the volume injected into the arm is 1.1 ml.
- At day 270 study participants receives one intramuscular injection of 0.5 ml Pneumo Novum + 0.1 ml test drug(CPG 7909)/placebo. In all cases, the volume injected into the arm is 1.1 ml.

Investigators and participants are not aware of whether experimental or control injection is administered. The volume and appearance of each injection product are identical. The exact product number of each test drug/placebo and batch number prepared by the hospital pharmacy will be recorded in the individuals CRF as well as the volume of any remaining fluid in the syringe .

Immunization and follow-up is conducted by investigators and study nurses at the Department of Infectious Diseases at Skejby Hospital, Aarhus University Hospital.

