**PRIMARY ENDPOINTS:**

*At six months after 2nd vaccination with Prevenar.*

- Pneumococcal vaccine high responders defined as 2-fold increase and IgG levels ≥1 µg/mL to at least 5 of 7 pneumococcal serotypes (by quantitative IgG measurements)

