**SECONDARY ENDPOINTS:**

**IMMUNOGENICITY**

*At three months after 1st vaccination with Prevenar.*

- Pneumococcal vaccine high responders defined as 2-fold increase and IgG levels ≥1 µg/mL to at least 5 of 7 pneumococcal serotypes (by quantitative IgG measurements)
- Opsonophagocytic activity for serotypes 6B, 14, 19F and 23F expressed as titers
- Serotype-specific antibody response defined as 2-fold increase and IgG levels ≥1 µg/mL
- Serotype-specific antibody response defined as change in IgG levels

*At six months after 2nd vaccination with Prevenar.*

- Opsonophagocytic activity for serotypes 6B, 14, 19F and 23F expressed as titers
- Serotype-specific antibody response defined as 2-fold increase and IgG levels ≥1 µg/mL
- Serotype-specific antibody response defined as change in IgG levels
- Cellular immune response

*At one month after vaccination with Pneumo Novum.*

- Pneumococcal vaccine high responders defined as 2-fold increase and IgG levels ≥1 µg/mL to at least 5 of 7 pneumococcal serotypes (by quantitative IgG measurements)
- Opsonophagocytic activity for serotypes 6B, 14, 19F and 23F expressed as titers
- Serotype-specific antibody response defined as 2-fold increase and IgG levels ≥1 µg/mL
- Serotype-specific antibody response defined as change in IgG levels
- Geometric Mean Antibody Concentrations With the Standard Enzyme Immunoassay for serotypes 1, 4, 7F, 9V, 14, 18C and 19F

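### The last blood sample is scheduled by study day and not by the third injection, so the one-month post-Pneumo Novum endpoints may rest on samples taken 0 to 90 days after it

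*Protocol*

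**What the plan says.** The endpoints are anchored to injections. The primary endpoint is read "At six months after 2nd vaccination with Prevenar" (Primary Endpoints). The last group of secondary endpoints is read "At one month after vaccination with Pneumo Novum" (Secondary Endpoints, Immunogenicity). That group holds the high-responder proportion, opsonophagocytic titres, two serotype-specific response measures and geometric mean concentrations.

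The visits are anchored to study day:

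- Vaccines and Test Drug/Placebo Injections: "All subjects are dosed at 0, 90 and 270 days".
- Procedures: "A concluding visit is scheduled at day 300".
- Schedule of Assessments, column headers: third injection at day 270 ± 30, one follow-up at day 270 ± 30, another at day 300 ± 30.
- Schedule, footnote 4, on the two late follow-ups: "Follow-up day 270 and day 300 is allowed to vary by 30 days".

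The order of sample and injection is stated for the first dose ("Blood samples for baseline parameter measurements will be drawn before proceeding to immunization", Procedures) and for the second ("Follow-up is done before proceeding to 2nd vaccination", footnote 3). It is not stated for the third.

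The header of the day 270 injection column refers to footnote 2, which reads "Day 90 follow-up and vaccination can vary by 14 days". That footnote mentions neither day 270 nor 30 days.

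**The concern.** An endpoint defined by time since injection needs a sampling window measured from that injection. Here the injection and the sample each have a window of ± 30 days around study days only 30 days apart, so the two windows overlap from day 270 to day 300.

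Samples taken at very different points on the response curve would therefore carry the same visit label. The protocol's own Background gives reasons to care: it describes a booster response when the polysaccharide vaccine follows the conjugate, and rapid loss of titre after polysaccharide vaccine. A sample at two weeks and one at eleven weeks would not measure the same quantity.

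At stake is what the last time point means and how precise it is. The sample size is not affected, because it is built on the primary endpoint.

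**Working it through.** **Inputs** (Schedule of Assessments, column headers)

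| Event | Window | Study days |
|---|---|---|
| Second injection | 90 ± 14 | 76 to 104 |
| Third injection | 270 ± 30 | 240 to 300 |
| Day 270 follow-up | 270 ± 30 | 240 to 300 |
| Day 300 follow-up | 300 ± 30 | 270 to 330 |

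**Nominal intervals.** 270 − 90 = 180 days (six months) and 300 − 270 = 30 days (one month). At the centre of every window, the schedule matches the endpoint definitions.

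**Range allowed for the last sample.** Shortest interval = earliest sample − latest injection. Longest interval = latest sample − earliest injection.

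- With the header's ± 30 for the injection: 270 − 300 = −30 days, and 330 − 240 = +90 days.
- With footnote 2's ± 14 for the injection (days 256 to 284): 270 − 284 = −14 days, and 330 − 256 = +74 days.

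**One window alone is enough.**

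- Injection exactly on day 270: 270 − 270 = 0 to 330 − 270 = 60 days.
- Follow-up exactly on day 300: 300 − 300 = 0 to 300 − 240 = 60 days.
- On the most generous reading, where the follow-up moves with the injection and keeps its tolerance: 30 ± 30 = 0 to 60 days.

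The injection date itself stays inside the permitted range in all three cases.

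**Unremarkable dates.** Injection on day 285 and visit on day 300: 300 − 285 = 15 days. Injection on day 250 and visit on day 325: 325 − 250 = 75 days. All four dates are within their windows.

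**The primary sample, for comparison.**

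- Since the second injection: 240 − 104 = 136 to 300 − 76 = 224 days, against 180.
- Relative to the third injection: 0 days if the two day 270 columns are one visit. Only if that visit is split does the range become 240 − 300 = −60 to 300 − 240 = +60 days (−44 to +44 with ± 14 for the injection).

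**The case against.** **The endpoint definition already excludes bad samples.** A sample drawn before or on the day of the third injection is plainly not one month after it. This stands, and it makes −30 a literal bound and not an expected event. It does nothing about the spread between a few days and 90 days, where the definition gives no tolerance.

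**Analysis windows belong in the SAP, and the trial is randomised and blinded.** The SAP is not shown and may deal with mistimed samples. Timing should not differ systematically between arms, so the main harm is to precision and interpretation. Both points stand. But a SAP can only label or exclude a mistimed sample. It cannot supply a one-month sample that was never drawn, and only 94 participants are planned.

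**A stronger reading concerns the primary endpoint.** A reader might infer that the primary sample can be drawn up to 60 days after the booster and so measure the wrong response. The documents do not support this. The table groups columns by type of procedure, so day 90 also appears twice, and footnote 3 shows that pair to be one attendance. The two day 270 columns share a nominal day and a window in the same way, and no section describes two attendances. The endpoint wording places the six-month reading before the booster. What is left is an unstated order within one visit.

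**A reader might also want the day 270 sample timed from the second injection.** That would conflict with drawing it before the third injection on unchanged injection dates. With injections on days 104 and 240, a pre-injection sample is at most 136 days after the second. With injections on days 104 and 270, the 180-day mark is day 284, which is after the third.

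**Conclusion.** The point holds for the concluding sample and should be fixed. As written, the one-month post-Pneumo Novum endpoints may rest on samples from 0 to 90 days after the injection (literally −30 to +90), or up to +74 if footnote 2 governs the injection. The problem survives every reading of the windows tried above.

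This rests on the column headers as printed and on day 300 ± 30 being counted from day 0. These are permitted ranges. The documents do not show how visits will actually be booked, so no number of affected participants can be given.

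The missing order rule at day 270 is a lesser matter of clarity, since the intent can be inferred. The mismatch between the day 270 header and footnote 2 looks clerical, but the two must be reconciled.

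**What to change.** 1. In the Schedule of Assessments, count the concluding follow-up from the actual date of the third injection: nominally 30 days, with a tolerance below 30 so that the injection date cannot fall inside it. As an illustration, the 14 days already used at day 90 would give 30 − 14 = 16 to 30 + 14 = 44 days.
2. Extend the rule of footnote 3 to the third dose: the day 270 samples are drawn at the same visit as the third injection and before it.
3. Reconcile the day 270 injection header with footnote 2.
4. Leave the injection dates as planned, and do not add a separate day 270 sampling window counted from the second injection. Record the actual interval since the second injection (136 to 224 days allowed) and report its distribution by arm.

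The cost is an edit to the table and footnotes and slightly tighter booking of the last visit, with no added visits. After a late third injection the last visit could fall somewhat later than now: with the illustrative 14 days, 300 + 44 = day 344 against the present limit of day 330.
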